### Feasibility assessment

2.7

The feasibility of this protocol will be assessed based on the recruitment rate, completion rate, and compliance with medication. The recruitment rate will be presented as a percentage giving the total number of registered participants in proportion to the total number of screened subjects. The completion rate will be presented as a percentage giving the number of subjects who completed the study in proportion to the total number of registered participants. The compliance with medication will be presented as a percentage giving the doses taken by the subjects in proportion to the target doses.

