#### Primary outcome

2.6.1

The primary outcome is the change in total nasal symptom score (TNSS). TNSS will be recorded in participants’ diaries every day before bedtime using a mobile application. A 4-point severity scale (no symptoms, 0; mild, 1; moderate, 2; and severe, 3) will be used.^[25]^ Using 4 weeks of TNSS scores, we will analyze the differences in the effects of SCRT and cetirizine, and the duration of the effects of each medication.

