### Sample size

2.10

No clinical trial has been conducted to evaluate the effects of SCRT on the TNSS for patients with AR. Therefore, we adapted the minimum number of subjects recommended for a preliminary study in the field of life sciences, 12 subjects in each group, for 24 subjects in total.^[30]^ Anticipating a dropout rate of 20%, the target of the recruitment is set to 15 subjects in each group, or 30 subjects in total.

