### Statistical analysis

2.11

An independent statistician who is blinded to the randomized allocation of participants will carry out the statistical analysis. Measured variables will be assessed using the full analysis set based on intention-to-treat principles, including all randomized participants who completing the trial without violating any of the exclusion criteria and for whom a complete set of data is available. The per-protocol analysis set will be used for the sensitivity analysis.

The demographic characteristics and baseline data of both groups will be summarized by means and standard deviations for the continuous variables, and frequencies and percentages will be presented for categorical variables. Baseline differences between groups will be assessed using independent *t* tests or Mann–Whitney *U* tests for continuous variables, and the chi-squared test or Fisher exact test for categorical variables. Differences in the primary and secondary outcomes will be analyzed using one-sided independent *t* tests. To demonstrate noninferiority, we will check whether the lower limit of the 2-sided 95% CI of the difference of the primary outcome between the 2 groups is greater than the noninferiority margin. The analysis will be presented as a difference with an associated 95% CI. To determine whether statistically significant differences exist between the groups, differences in the primary and secondary outcomes will be analyzed using a mixed effects model for repeated measurement. Subgroup analyses will also be conducted to investigate the difference in treatment effect according to the type of cold–heat pattern identification questionnaire, each symptoms of AR, and the results of Nasal Endoscopy Index. The level of significance will be set at 0.05 (2-tailed), and all analyses will be performed using SAS (V.9.4; SAS Institute).

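### Completion of the daily app diary, the source of the primary outcome, is not a feasibility measure, and the 20% dropout allowance leaves no reserve for the complete-data condition

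*Protocol article*

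**What the plan says.** The protocol article bears on this point in four places.

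- **2.7 Feasibility assessment.** "The feasibility of this protocol will be assessed based on the recruitment rate, completion rate, and compliance with medication". Each rate is then defined. Recruitment is registered over screened participants. Completion is a percentage "giving the number of subjects who completed the study in proportion to the total number of registered participants". For the third: "The compliance with medication will be presented as a percentage giving the doses taken by the subjects in proportion to the target doses".
- **2.6.1 Primary outcome.** "TNSS will be recorded in participants’ diaries every day before bedtime using a mobile application". The diary is then used as follows: "Using 4 weeks of TNSS scores, we will analyze the differences in the effects of SCRT and cetirizine". The abstract gives the primary contrast as the change from baseline to week 2.
- **2.10 Sample size.** Twelve per group is taken as a recommended minimum for a preliminary study, and then: "Anticipating a dropout rate of 20%, the target of the recruitment is set to 15 subjects in each group".
- **2.11 Statistical analysis.** The full analysis set is limited to randomized participants who complete the trial, violate no exclusion criterion, and "for whom a complete set of data is available". A mixed effects model for repeated measurement is also named.

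Section 2.4.2 excludes people who cannot use the app for daily recording.

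**The concern.** The Introduction gives the purpose as validating a protocol, and the Discussion expects the findings to support a full-scale trial. Whether the primary endpoint can be captured day by day is central to that purpose. Section 2.7 nevertheless lists three measures, defines each, and leaves out the instrument that carries the primary outcome. A participant can take every dose, attend the last visit and count fully in all three rates with a diary full of gaps. The app-related exclusion screens for ability to use the app; it does not measure whether entries are made.

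The sample size has a related gap. The allowance in 2.10 is spent entirely on dropout, whereas 2.11 also removes completers whose data are incomplete. Those losses come on top of dropout and nothing is set aside for them.

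**Working it through.** **Inputs from the document:** 12 per group, 20% dropout, 15 per group (2.10); 4 weeks of daily scores, so 28 entries (2.6.1); about 14 entries on treatment, from 2 weeks of medication (2.5); the complete-data condition (2.11).

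**Assumed, because the document gives no figure:** the daily entry rate p, independence of misses between days, and the share c of completers whose data count as complete.

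**1. The plan's own figure.** 12/(1 − 0.20) = 15 per group and 24/(1 − 0.20) = 30 in total. It reproduces exactly. In reverse, 15 × 0.80 = 12.0.

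**2. Reserve for incomplete data in one arm** (15 − dropouts − 12):

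| Dropouts | Completers | Incomplete completers that still leave 12 |
|---|---|---|
| 0 | 15 | 3 |
| 1 | 14 | 2 |
| 2 | 13 | 1 |
| 3 (the planned 20%) | 12 | 0 |

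**3. Effect of c, with 20% dropout.** Expected in the analysis = 15 × 0.80 × c = 12c. Recruitment needed to keep 12 = 12/(0.80c), rounded up. The chance of at least 12 is the upper tail of a binomial with n = 15 and probability 0.80c.

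| c | Expected per arm | Needed per arm | Chance of at least 12 of 15 |
|---|---|---|---|
| 1.00 | 12.0 | 15 | 0.648 |
| 0.95 | 11.4 | 16 | 0.498 |
| 0.90 | 10.8 | 17 | 0.358 |
| 0.80 | 9.6 | 19 | 0.153 |

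The first row is dropout alone, so the effect of incomplete data is the fall from 0.648.

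**4. Strict reading: every daily entry required.** Then c = p^28, or p^14 if only the treatment weeks count. With 24 completers, the number without a gap over 28 days is 24 × p^28.

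| p | p^14 | p^28 | Without a gap over 28 days, of 24 |
|---|---|---|---|
| 0.99 | 0.869 | 0.755 | 18.1 |
| 0.98 | 0.754 | 0.568 | 13.6 |
| 0.95 | 0.488 | 0.238 | 5.7 |
| 0.90 | 0.229 | 0.052 | 1.2 |

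**5. Lenient reading: at least 4 of 7 entries in a baseline week and in week 2.** At p = 0.90 the chance of at least 4 of 7 is 0.9973 in one week. For both weeks it is 0.9973² = 0.9946, or 23.9 of 24 completers.

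**6. The feasibility rates.** The numerators in 2.7 are registered participants, participants who finished and doses taken. None changes with p, so the three percentages are the same in every row of step 4.

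**The case against.** The strongest reply is that the loss of participants is a product of the assumptions. The document does not say that complete data means every diary entry; a baseline and a week-2 value for each outcome would be an equally natural reading, and one missed evening would then remove nobody. Independent misses are also unfavourable to the plan: if misses cluster in a few people, more diaries are free of gaps at the same average rate. This stands, and it is why the tables in steps 3 and 4 show a range and not an estimate.

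A reader might infer that 12 per group can be reached only if no completer misses an entry. The document does not support that. It would need both three dropouts in the arm and the strictest reading of the complete-data condition. Nor is 12 stated as a number to be analysed. It is a recommended pilot minimum with no power or precision target attached, although inflating it for dropout implies a target after losses.

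A reader might also infer that the trial would declare itself feasible without noticing a failed diary. Section 2.7 sets no threshold and only presents percentages. Monitors check whether data are adequately recorded (2.12), visits are weekly, and the size of the analysis set would itself show heavy losses under a strict reading. Failure would probably be seen, but diary completion would still not be a planned feasibility result.

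Finally, rules for weekly means and minimum entries are commonly left to the full protocol or analysis plan, so their absence from an article is no finding. That is accepted. What is at issue is what the article does fix: a defined list of feasibility measures and a condition for entry to the analysis set. The mixed model does not remove the second problem, because it can use partial series only from participants whom 2.11 admits.

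**Conclusion.** The point holds in two parts of different strength.

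The first needs no assumption. None of the three defined feasibility measures counts diary entries, although the diary is the only stated source of the primary outcome. The feasibility results as planned would not show whether the endpoint can be collected.

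The second is conditional. At 20% dropout an arm has exactly 12 completers and no reserve, so each one excluded for incomplete data takes it below 12; with fewer dropouts there is room for one to three. The size ranges from almost no loss (4-of-7 rule, 90% daily entry) to about 10 of 24 completers (every entry required, 98% daily entry over 28 days, independent misses), and more at lower entry rates. The document cannot settle where in that range the trial would fall.

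This is a design improvement that should be made; it does not show that the stated sample size is miscalculated.

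**What to change.** In 2.7, add diary completion as a fourth feasibility outcome: daily TNSS entries made over entries due, by arm and by period (run-in if the diary is kept then, treatment, follow-up), together with the percentage of participants who have an evaluable baseline-to-week-2 TNSS change. Also report how many people were screened out because they could not use the app.

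In 2.6.1 and 2.11, state that a participant with isolated missed entries stays in the full analysis set. One way is to compute weekly TNSS means from a prespecified minimum number of entries and let partial series enter the mixed model already planned. Four of 7 is an example of such a minimum; it does not come from the document, and another could be chosen in advance.

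The cost is one rate from data the app would already hold and a sentence or two in the analysis text, with no added participants or visits. The drawback is that reported feasibility may look less favourable.

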### Randomization

2.8

Block randomization is performed to assign the same number of subjects to the SCRT or cetirizine group. Thirty participants will be assigned to each group with the same probability that each individual will be selected. An expert on statistics who is not in contact with the participants will generate randomization serial numbers using the statistical program Strategic Applications Software (SAS, V.9.4; SAS Institute, Cary, NC). Before the random assignment, all participants will be informed that they will be allocated to one of 2 groups.

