**Methods and analysis::**

This is a randomized, open-label, cetirizine-controlled clinical trial. A total of 30 AR patients who have signed informed consent forms will be recruited and randomly assigned to SCRT or cetirizine groups at a 1:1 ratio. The participants will visit the clinical research center every week and receive SCRT granules or cetirizine tablets. SCRT will be taken twice daily, cetirizine will be taken once daily, and treatment medication will be taken for 2 weeks. Data will be collected at baseline, at week 2, and at week 4 after random allocation. The primary outcome will be the mean change in the total nasal symptom score from baseline to week 2. Secondary outcome measures will include the mini Rhinoconjunctivitis Quality of Life Questionnaire and total serum immunoglobulin E. To assess the safety of SCRT, a liver and renal function test will be conducted before and after treatment, and the participants will be asked about any occurrence of adverse events at every visit. The recruitment rate, completion rate, and medication adherence will also be calculated to assess feasibility.

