### Trial design and setting

2.2

This is a randomized two-parallel-arm open-label cetirizine-controlled comparative effectiveness study. This study will be conducted at Woosuk Korean Medicine Medical Center, Jeonju, Republic of Korea. The study has 2 arms: the SCRT treatment group and the cetirizine control group. A total of 30 participants will be recruited for this trial. Cetirizine will be used as an active control to compare the effectiveness of SCRT on AR patients whose symptoms are not controlled by conventional medication. The total study period will be 5 weeks. It consists of a week run-in period after screening, 2 weeks of medication, and 2 weeks of follow-up after medication is stopped.

The detailed design is summarized in Fig. 1 and Table 1. The study protocol (version 1.3) follows the Standard Protocol Items: Recommendations for Interventional Trials (SPIRIT) guidelines (see Additional File 1).

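### Section 2.8 assigns thirty participants to each group, twice the 15 per group (30 in total) that the sample size section plans

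*Protocol article*

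**What the plan says.** Four places in the protocol article bear on the number randomised.

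- **Section 2.8, Randomization:** "Thirty participants will be assigned to each group". The sentence goes on to speak of equal probability of selection. The preceding sentence says that block randomisation is used to make the two groups equal in size.
- **Section 2.10, Sample size:** the starting point is "12 subjects in each group, for 24 subjects in total", taken from a recommended minimum for preliminary studies. After an allowance for 20% dropout, "the target of the recruitment is set to 15 subjects in each group, or 30 subjects in total".
- **Section 2.2, Trial design and setting:** "A total of 30 participants will be recruited for this trial", in two arms.
- **Abstract, Methods and analysis:** 30 patients in total, "randomly assigned to SCRT or cetirizine groups at a 1:1 ratio".

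Only section 2.10 states 15 per group in so many words. The abstract and section 2.2 give the total of 30. The figure of 15 follows from the 1:1 ratio in the abstract, and from the two arms in section 2.2 with the equal group sizes promised in section 2.8.

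**The concern.** Section 2.8 is where the article describes how the randomisation numbers are generated, so a reader would look there for the number per arm. The number given is the trial total, attached to each group. Taken literally, it describes a trial of twice the planned size.

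What is at stake is a clear statement of the target. If 30 participants are recruited, the trial has met its target under section 2.10 but has reached only half of the target implied by section 2.8 (30/60 = 50%). The recruitment and completion rates in section 2.7 do not use the target as a denominator, so their definitions are unaffected. But readers who use this feasibility trial to plan a full-scale one need a single unambiguous planned size.

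**Working it through.** **Inputs**

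- Evaluable participants per group: 12 (section 2.10)
- Anticipated dropout: 20% (section 2.10)
- Number of arms: 2 (section 2.2)
- Allocation: 1:1 (abstract), equal numbers (section 2.8)
- Per-group number under question: 30 (section 2.8)

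**Step 1. Reproduce the plan's own target.** Recruitment per group = evaluable / (1 − dropout) = 12 / (1 − 0.20) = 12 / 0.80 = 15. Total = 2 × 15 = 30. Both figures in section 2.10 reproduce exactly. The cruder inflation, 12 × 1.20 = 14.4, also rounds up to 15 per group, so the choice of formula does not matter here.

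**Step 2. Read section 2.8 literally.** 30 per group × 2 groups = 60. Ratio to the stated total: 60 / 30 = 2.0.

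**Step 3. Ask whether 30 per group could come from the stated inputs.**

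- To go from 30 randomised to 12 evaluable per group, dropout would have to be 1 − 12/30 = 0.60, that is 60% against the 20% stated.
- At the stated 20% dropout, 30 per group would leave 30 × 0.80 = 24 evaluable per group, against the 12 stated.

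Neither agrees with section 2.10.

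**Step 4. Compare all the statements.**

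| Place | Per group | Total |
|---|---|---|
| Abstract | 15 (implied by 1:1) | 30 (stated) |
| Section 2.2 | 15 (implied by two equal arms) | 30 (stated) |
| Section 2.10 | 15 (stated and derived) | 30 (stated) |
| Section 2.8 | 30 (stated) | 60 (implied) |

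Three places agree, and one of them shows its derivation. Section 2.8 stands alone. Reading its number as 15 per group brings all four into line.

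**The case against.** The strongest reply is that this is a slip of wording and not a second sample size. The rest of the sentence in section 2.8 concerns equal probability of assignment, and thirty is exactly the trial total given elsewhere. The natural intended meaning is that the thirty participants are assigned to either group with equal probability. Section 2.10 gives the derivation, the per-group number and the total without ambiguity, so anyone preparing the list would have the right target available. This reply stands as an explanation of how the sentence arose. It does not make the sentence correct: a per-group number stated in the randomisation section is still twice the planned one. No analysis plan or fuller protocol could make the sentence agree with section 2.10 as it is worded.

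A reader might go further and draw either of two inferences that the document does not support.

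- **That the allocation list and envelopes would be built for 60.** The article shows no list and gives no list length. It does not show that the statistician works from this sentence. What is established is a wrong written number, not a wrong list.
- **That cutting a list of 60 at 30 would unbalance the arms, for example 16:14.** That depends on the block size, which the article does not give (and an article commonly leaves to the full protocol). With blocks of 2, 6 or 10, the 30th place ends a block and the split is 15:15. With blocks of 4, 30 falls mid-block (30 = 7 × 4 + 2) whatever length the list was written for. Any imbalance would come from the assumed block size and not from the contradiction described here.

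**Conclusion.** The point holds as an internal contradiction. Section 2.8 gives a per-group number of 30, implying 60 in total. The abstract and sections 2.2 and 2.10 give or imply 15 per group and 30 in total. The discrepancy is a factor of two, and the number in section 2.8 is the one to correct, because only the figure in section 2.10 follows from stated inputs.

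The conclusion rests on two equal arms and on the 12 per group and 20% dropout of section 2.10, all of which the article states. That the sentence is a drafting slip is a judgement, though a likely one. The correction leaves the planned sample size, the allocation ratio and the analysis unchanged. It is nevertheless worth making, because the number stands in the section that governs randomisation.

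**What to change.** Reword the sentence in section 2.8 along these lines: *30 participants in total will be allocated 1:1, 15 to each group.* If the intention was also to state the chance of assignment, add that each participant is equally likely to be allocated to either group. Then confirm that the allocation list matches the target of 30.

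The cost is one sentence and one check.

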### Blinding

2.9

To avoid selection bias, the randomization of serial numbers will be managed using sealed envelopes and a locked cabinet. Investigators will open a sealed envelope when a participant is enrolled. The experimental drug in this trial is an herbal medicine that is provided in granules, while the control medication is a drug that comes in tablets. Because patient blinding is not possible, the trial is designed as open label. Although the subjective symptoms of subjects is the main outcome, total serum IgE and Nasal Endoscopy Index will also be examined. The Nasal Endoscopy Index test will be conducted by an investigator who has not been informed about the random assignment and medication and does not know to which group each subject is assigned. This process is intended to reduce the possibility of bias by the evaluators.

### Sample size

2.10

No clinical trial has been conducted to evaluate the effects of SCRT on the TNSS for patients with AR. Therefore, we adapted the minimum number of subjects recommended for a preliminary study in the field of life sciences, 12 subjects in each group, for 24 subjects in total.^[30]^ Anticipating a dropout rate of 20%, the target of the recruitment is set to 15 subjects in each group, or 30 subjects in total.

### Statistical analysis

2.11

An independent statistician who is blinded to the randomized allocation of participants will carry out the statistical analysis. Measured variables will be assessed using the full analysis set based on intention-to-treat principles, including all randomized participants who completing the trial without violating any of the exclusion criteria and for whom a complete set of data is available. The per-protocol analysis set will be used for the sensitivity analysis.

The demographic characteristics and baseline data of both groups will be summarized by means and standard deviations for the continuous variables, and frequencies and percentages will be presented for categorical variables. Baseline differences between groups will be assessed using independent *t* tests or Mann–Whitney *U* tests for continuous variables, and the chi-squared test or Fisher exact test for categorical variables. Differences in the primary and secondary outcomes will be analyzed using one-sided independent *t* tests. To demonstrate noninferiority, we will check whether the lower limit of the 2-sided 95% CI of the difference of the primary outcome between the 2 groups is greater than the noninferiority margin. The analysis will be presented as a difference with an associated 95% CI. To determine whether statistically significant differences exist between the groups, differences in the primary and secondary outcomes will be analyzed using a mixed effects model for repeated measurement. Subgroup analyses will also be conducted to investigate the difference in treatment effect according to the type of cold–heat pattern identification questionnaire, each symptoms of AR, and the results of Nasal Endoscopy Index. The level of significance will be set at 0.05 (2-tailed), and all analyses will be performed using SAS (V.9.4; SAS Institute).

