#### Exclusion criteria

2.4.2

Participants will not be eligible if they meet one or more of the following criteria:

1.A previous history of nose-related or allergy-related disease and treatment, including any of the following:A.Congenital deviated nasal septum, nasal polyps, acute or chronic sinusitis, asthma symptomsB.Use of topical decongestants or cromolyn sodium within the previous 3 daysC.Use of antihistamines or anticholinergics within the previous weekD.Use of intranasal or oral steroids within the previous 2 weeksE.Use of leukotriene receptor antagonists within the previous 4 weeksF.Use of Korean medicine treatment (acupuncture, moxibustion, herbal medicine, cupping, etc) for the treatment of AR within the previous monthG.Receipt of immunotherapy within the previous 5 years2.Presence of serious medical conditions that could interfere with clinical trial participation, including any of the following:A.Hypertension (systolic blood pressure greater than 160 mm Hg or diastolic blood pressure greater than 100 mm Hg)B.Diabetes mellitus (fasting blood glucose greater than 126 mg/dL)C.Renal dysfunction (serum creatinine level more than twice the normal range)D.Liver function abnormality (alanine aminotransferase or aspartate aminotransferase levels that are more than twice the upper limit of the normal range)E.Serious hyperlipidemia, anemia, active tuberculosis, thyroid disease, or other serious inflammatory or systemic diseaseF.Past or present history of malignant tumors3.Pregnancy or breast-feeding4.Other; ineligible for participation as judged by the investigator:A.Those who cannot use mobile applications to record symptoms of AR daily.

After voluntary consent to the study, potential participants will be screened using MAST at the first visit to determine if the rhinitis is allergic. In the MAST, the amount of IgE present in the serum is measured to determine the cause of 92 kinds of respiratory and food allergies and to determine the severity of the allergic reaction.^[24]^ To rule out the possibility of suppression of allergic reaction, drugs containing antihistamines and steroids will be stopped a week before the test. At any time during the clinical trial, the participant may voluntarily withdraw from the clinical trial or can be dropped at the researcher's discretion.

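### The set labelled full analysis set on intention-to-treat principles is in fact a completer set, so the main comparison leaves out randomised participants on grounds known only after allocation

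*Protocol article*

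**What the plan says.** Section 2.11 (Statistical analysis) opens with the label: "Measured variables will be assessed using the full analysis set based on intention-to-treat principles". The same sentence then gives the membership rule: "including all randomized participants who completing the trial without violating any of the exclusion criteria and for whom a complete set of data is available". Only one sensitivity analysis is named, and it is on another set: "The per-protocol analysis set will be used for the sensitivity analysis". The article gives no criteria for that set. Section 2.11 also plans a mixed effects model for repeated measurements and a noninferiority comparison on the primary outcome.

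Three other places bear on who would be left out:

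- Section 2.4.2 (Exclusion criteria) says that at any time "the participant may voluntarily withdraw from the clinical trial or can be dropped at the researcher's discretion".
- Section 2.9 (Blinding) states that the trial is open label.
- Section 2.10 (Sample size) takes "12 subjects in each group, for 24 subjects in total", allows for 20% dropout, and concludes that "the target of the recruitment is set to 15 subjects in each group, or 30 subjects in total".

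**The concern.** An intention-to-treat set keeps participants in the arm to which they were randomised, whatever happens afterwards. Two of the three conditions in section 2.11, finishing the trial and having complete data, are outcomes of the trial itself. Once membership depends on them, the two arms are no longer protected by randomisation. If people leave one arm because it did not help or was poorly tolerated, that arm looks better than it is.

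In this trial both the participant and the treating researcher know the allocation, and both can end participation. The primary outcome is a self-reported nasal symptom score. The results are meant to support a full-scale trial, so a treatment difference or SD taken from selected completers would carry forward into that design.

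**Working it through.** **1. Label against rule.**

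| Condition in section 2.11 | When it is known | Compatible with intention-to-treat? |
|---|---|---|
| Randomised | At allocation | Yes |
| No exclusion criterion violated | Mostly before allocation (section 2.4.2 lists largely screening conditions) | A departure, but mostly not driven by response |
| Completed the trial | After allocation | No |
| Complete set of data | After allocation | No |

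No other section of the article corrects the rule. Read literally, completing the trial includes the two-week follow-up after medication stops (section 2.2). Someone who gave every score needed for the baseline-to-week-2 primary outcome and then missed week 4 would therefore also be left out.

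**2. How many are lost.** Inputs from section 2.10: 12 per group, 20% dropout.

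- The plan's own figure: 12 / (1 − 0.20) = 15 per group, 30 in total. It reproduces exactly.
- Completers at that dropout: 30 × 0.80 = 24, so about 6 of 30 are excluded. The complete-data condition can only lower the 24.
- What counts as complete is not defined. One reading, taken as an assumption, is all 28 daily diary entries (4 weeks, section 2.6.1). With independent misses at 1% per day, 0.99^28 = 0.755 and 24 × 0.755 ≈ 18 remain. At 2% per day, 0.98^28 = 0.568 and 24 × 0.568 ≈ 14 remain.

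**3. What selective loss could do.** Assumptions: normal outcome, no true difference, 15 per arm, 3 lost per arm. Losses in the other arm are uninformative unless stated.

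- Losses uninformative, or the 3 worst lost from both arms: expected shift in the difference 0.
- In one arm, one loss is the worst responder and the other two are random: the expected extreme of 15 standard normals is 1.736, so the shift is 1.736 / 14 = 0.12 SD.
- In one arm, all three losses are the three worst: the expected values of the three extremes are 1.736, 1.248 and 0.948, so the shift is (1.736 + 1.248 + 0.948) / 12 = 0.33 SD. The large-sample formula φ(0.842) / 0.8 = 0.280 / 0.8 gives 0.35 SD. The same formula gives 0.19 SD at 10% loss and 0.50 SD at 30%.

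**4. Scale.** The 95% CI half-width for a difference in means, in SD units, is t(0.975; 2n − 2) × √(2/n).

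- n = 12: 2.074 × 0.408 = 0.85.
- n = 15: 2.048 × 0.365 = 0.75.

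The one-arm worst case is therefore about two fifths of the half-width at 12 per arm (0.33 / 0.85 = 0.39).

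**5. Other planned analyses.** A conventional per-protocol set removes people from the full set. Starting from completers with complete data, it can only remove more, for example for low adherence or prohibited treatment. The mixed model can use participants with some visits or diary days missing, but under the section 2.11 rule they never reach it.

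**The case against.** The strongest reply is that this is a 30-person feasibility trial sized by a rule of thumb. It reports its completion rate (section 2.7), so attrition will be visible, and its analysis is done by an independent statistician blinded to allocation. Nothing in the documents shows that removals will differ between arms, and even the worst case above lies well inside the confidence interval. It is right that the bias is possible and not shown, and that its size and direction are unknown. But the statistician's blinding acts after participants have already left, and a completion rate shows how many left without restoring their data. Section 2.11 also plans significance tests and a noninferiority comparison on this set.

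It is fair, too, that exclusion for ineligibility rests mostly on pre-randomisation facts and is not the main problem. The mixed model would still run on completers; what it loses is the partial records.

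Three stronger readings are tempting but not supported:

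- **The per-protocol set contains almost the same people.** Its criteria are not given, and it could exclude more for low adherence or prohibited treatment. What can be said is that a conventional per-protocol set would not restore those already excluded.
- **Participants who stop for an adverse event vanish from the safety results.** Section 2.11 names no safety analysis, and section 2.13 covers safety separately, with adverse events checked at every visit. The point holds only if the measured variables of section 2.11 are meant to include the safety laboratory tests.
- **The researcher chooses who is analysed.** The clause in section 2.4.2 is a general withdrawal clause. It affects the analysis set only through the completion condition.

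**Conclusion.** The definition is wrong as written: section 2.11 puts an intention-to-treat label on a completer set. This follows from the text alone and rests on no assumption. At the plan's own dropout rate, at least 6 of 30 randomised participants are absent from the main analysis, and no analysis set described in the article brings them back.

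The effect on the treatment difference cannot be determined from the documents. Under a normal outcome and 3 losses per arm, the scenarios run from 0 to about 0.33 SD, the upper figure being a one-arm worst case and not a forecast. The half-width of 0.85 SD reflects sampling error only and does not allow for such a shift. The sample size arithmetic is unaffected, since 24 evaluable participants is consistent with a completer analysis.

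**What to change.** In section 2.11:

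- Define the full analysis set as all randomised participants, analysed as allocated, regardless of completion, adherence or missing diary days. If it is limited to those with at least one post-baseline nasal symptom score, label it modified intention-to-treat, because that condition is also met only after randomisation.
- Let the repeated-measures mixed model use all available data on that set.
- Keep the present completer definition for the per-protocol sensitivity set.
- If the measured variables are meant to include the safety laboratory tests, state that these are summarised in all participants who took study medication.

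The cost is a change of wording in the protocol and analysis plan. No extra participants or measurements are needed.
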